#### Secondary outcomes

Secondary outcomes including entomological indices, such as HI, CI, BI, PPH, and PPP and dengue viral infectivity rate, will also be analyzed by the above methods.

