**Methods/design:**

In this cluster randomized controlled, superiority trial, 30 clusters comprising one or more villages each (with approximately 170 households) will be allocated, in a 1:1:1 ratio, to receive either (1) three interventions (guppies, Sumilarv® 2MR, and COMBI activities), (2) two interventions (guppies and COMBI activities), or (3) control (standard vector control). Households will be invited to participate, and entomology surveys among 40 randomly selected households per cluster will be carried out quarterly. The primary outcome will be the population density of adult female *Aedes* mosquitoes (i.e., number per house) trapped using adult resting collections. Secondary outcome measures will include the House Index, Container Index, Breteau Index, Pupae Per House, Pupae Per Person, mosquito infection rate, guppy fish coverage, Sumilarv® 2MR coverage, and percentage of respondents with knowledge about *Aedes* mosquitoes causing dengue. In the primary analysis, adult female *Aedes* density and mosquito infection rates will be aggregated over follow-up time points to give a single rate per cluster. This will be analyzed by negative binomial regression, yielding density ratios.

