#### Sample size

The guppy fish and PPF interventions will be assessed by an entomology survey. A sample size of 10 clusters per arm and 40 HHs per cluster for the survey was devised using the Hemming and Marsh method [45]. The calculation assumed a mean of 0.1 adult female resting *Aedes* mosquitoes per HH in the intervention arms compared to 0.25 in the control arm for each collection. This assumption was based on the results from the earlier World Health Organization/Asian Development Bank guppy fish project in the same province [22], and to be conservative assumed no impact from the PPF in arm 1. The HHs will be randomly selected at each collection. The intracluster correlation (ICC) was assumed to be 0.01 based on previous studies [46–48]. Additionally, a sensitivity analysis was conducted up to the median value of ICCs for outcome variables (0.03) as found by an analysis conducted by Campbell et al. [49]. Our analysis determined that we would have between 91 to 75% power at ICC values between 0.01 to 0.03. The coefficient of variation in cluster sample size was assumed to be 0.1, and is expected be small as we plan to sample the same number of houses from each cluster. Under these assumptions the study will have 91–75% power to detect a difference at the 5% significance level.

COMBI activities will be evaluated through Knowledge, Attitudes, and Practice (KAP) surveys. A sample size of 10 clusters per arm and 20 HHs per cluster was devised, again using the Hemming and Marsh method [45]. The calculation assumed a 22.5% change in primary outcome indicators from 40 to 62.5% in intervention villages and no change in the control villages over the course of 1 year. Outcome indicators include:Percentage of respondents with knowledge about *Aedes* mosquitoes causing denguePercentage of HHs that keep guppy fish/PPF in water

This calculation was based on the results from the earlier projects done by Malaria Consortium (MC) in the region, and a recent unpublished MC KAP survey completed in six provinces and 30 villages in 2014. The ICC was assumed to be 0.01, and the coefficient of variation of cluster size assumed to be 0.1. Under these assumptions the study will have 90% power to detect a difference at the 5% significance level.

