### Entomology

A baseline survey was conducted prior to start of interventions. An endline survey will be conducted 1 year after the baseline. Two additional surveys during the dry season (4 months post intervention) and light rain (8 months post intervention – peak dengue season) will also be conducted. The schedule of the surveys took into account data from the previous guppy fish project [22]. The survey methodology was developed following the WHO guidelines for entomological collections [1]. Surveys will include indoor adult resting catches and larvae/pupae collection from water containers. The survey team consisted of experienced government staff who received 3 days’ training before beginning. All tools and materials were pre-tested during training. The same team will be used for each entomology survey. Houses within each cluster were selected using a random-number generator [50] applied to the village list managed by the village head.

The adult resting catch will be completed using a battery-powered, portable aspirator (Camtech, Phnom Penh, Cambodia) for 10 min per house in the bedrooms and living spaces, starting in the bedroom and aspirating up and down the wall (from floor to 1.5 m) around the home in a clockwise manner. The mosquitoes will be kept in a screw-top containers inside a cold box and transported to the provincial laboratory for identification to the species level for *Aedes*, otherwise to genus. All *Aedes* mosquitoes will be sexed. After identification they will be stored in a −20 °C freezer and taken to the United States Naval Medical Research Unit 2 (NAMRU-2) in Phnom Penh for confirmation. All *Aedes* females will be pooled and subjected to flavivirus rRT-PCR screening [51]. Flavivirus-positive pools will be further tested for dengue typing by semi-nested RT-PCR assay targeting the C and pre-M regions within the viral genome [52].

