#### Primary outcome

Adult female *Aedes* density will be summed over follow-up time points to give a single rate per cluster. This will be analyzed by negative binomial regression using the number of adults as the response, and the logarithm of the sampling effort (that is, person-time spent aspirating) as an offset. Hence, this analysis will yield density ratios. The primary analysis will not be adjusted, but secondary analysis will include an analysis adjusted for the baseline density.

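### Under the stated rule, the dengue infection rate, and the Container Index if the offset is kept literally, are analysed per house rather than per mosquito or per container

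*Protocol article*

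**What the plan says.** The Secondary outcomes paragraph under Statistical methods gives one rule: entomological indices "such as HI, CI, BI, PPH, and PPP and dengue viral infectivity rate, will also be analyzed by the above methods". The only method above it is the one for the primary outcome. There, adult female density is "summed over follow-up time points to give a single rate per cluster" and fitted by negative binomial regression with "the logarithm of the sampling effort (that is, person-time spent aspirating) as an offset". The paragraph closes: "Hence, this analysis will yield density ratios".

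The abstract applies the same rule to infection: "adult female *Aedes* density and mosquito infection rates will be aggregated over follow-up time points to give a single rate per cluster", followed by negative binomial regression and density ratios.

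The list under Secondary outcome measures uses several denominators: adult females for infection, containers for CI, houses for HI, BI and PPH, and persons for PPP. CI and BI share a numerator (positive containers), as do PPH and PPP (pupae).

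The Entomology section fixes aspiration "for 10 min per house in the bedrooms and living spaces" and says of the adult catch that all *Aedes* "females will be pooled and subjected to flavivirus rRT-PCR screening". The Sample size section says "we plan to sample the same number of houses from each cluster", namely 40 per cluster.

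**The concern.** An offset decides what a count model estimates. With log aspiration time as offset, the arm coefficient is a ratio of counts per minute of aspiration. That suits the adult catch. It does not suit outcomes defined per mosquito, per container or per person.

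Infection matters most. The first main hypothesis says that the combined intervention will lower both mosquito numbers and their infection rates. If the infection analysis moves whenever density moves, it adds no evidence on infection per mosquito: a pure density effect would be reported as success on both parts.

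For CI, the interventions can change the denominator itself, since the behaviours that COMBI promotes include burning or burying discarded containers. An analysis that ignores container numbers can show a lower CI when the share of containers infested has not changed.

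**Working it through.** The plan gives no figure for this point, so there is none to reproduce. The check is algebra, followed by a simulation.

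**Inputs from the Protocol article.** 10 minutes of aspiration per house; 40 houses per cluster per survey; three follow-up surveys (4, 8 and 12 months); 10 clusters per arm; planning densities of 0.10 (intervention) and 0.25 (control) females per house.

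**Inputs assumed for illustration.** 6.0 versus 4.2 containers per house; 30% of containers positive in both arms; infection prevalence of 5%. The documents give none of these.

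**1. The offset.** Aspiration time per cluster = 10 × 40 = 400 minutes per survey, and 400 × 3 = 1,200 minutes over follow-up. This is 10 × houses (120 house visits) and is the same in every cluster. In a log-link model a constant offset goes into the intercept, so every arm ratio becomes a ratio of counts per house.

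**2. Infection.** Infected females per house = density × prevalence. With prevalence p in both arms:

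(0.10 × p) / (0.25 × p) = 0.40, for any p.

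Per female tested, the ratio is p / p = 1.00. Counting positive pools instead of infected females also gives 0.40 if pool size is the same in both arms, because the number of pools then follows the number of females.

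**3. CI.** Positive containers per house = CI × containers per house. In the assumed example this is 0.30 × 6.0 = 1.80 in control and 0.30 × 4.2 = 1.26 in intervention. The ratio is 1.26 / 1.80 = 0.70, which is the BI ratio; the CI ratio is 0.30 / 0.30 = 1.00. With CI equal in the two arms, the fitted ratio equals the share of containers remaining: 0.90 if 10% are removed, 0.50 if 50% are removed.

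**4. PPP.** PPP ratio = PPH ratio × (persons per house in control / persons per house in intervention). Randomisation creates no systematic difference in household size, so the last factor should be near 1.

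**5. HI, BI and PPH.** Their denominator is houses, to which the offset is proportional. Their ratios keep their meaning.

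**6. Simulation.** 300 data sets, 10 versus 10 clusters, negative binomial dispersion fixed at 0.1, and no true effect on the outcome as defined. Median fitted ratios:

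| Outcome | Aspiration-time offset | Own denominator |
|---|---|---|
| Infection | 0.40 | 1.02 (females) |
| CI | 0.70 | 1.00 (containers) |
| PPP | 1.04 | 1.04 (persons) |

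Within each data set, the CI model with the aspiration offset gave the BI ratio, and the PPP model the PPH ratio, to within 1e-14.

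**The case against.** The strongest reply is that the rule cannot be applied word for word. The primary model's response is the adult count, so it must be replaced for pupae or containers, and an analyst may replace the offset too. Larvae and pupae are not collected by aspiration, so aspiration time is not their sampling effort. The outcome list names each denominator, and survey teams record the number of containers. On that reading CI does not turn into BI. The article is also condensed, and its Dissemination policy section refers to a separate full protocol and statistical code.

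Much of this stands for the larval indices. A reader might infer that CI and PPP could never be estimated as defined; the documents do not support that, because a sensible substitution is open and nothing forbids it. It is weaker for infection. Nothing states the substitution, the abstract puts infection and density in one analysis that yields density ratios, and aspiration is how those females are caught. Condensing excuses an omission, but here a rule is stated and it gives the wrong quantity.

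Two other inferences also go too far:

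- **That HI and CI are invalid because a negative binomial model is used for bounded proportions.** With the right denominator, a log-link count model still estimates a ratio of proportions. What remains is variance modelling: dispersion near zero gives a Poisson model, which is conservative for bounded counts.
- **That the infection comparison has some particular low power, or that a false significant result is likely.** Both depend on infection prevalence, which the documents do not give. The article claims no power for infection.

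**Conclusion.** The point holds for infection on the rule as written, and for CI if the aspiration offset is kept literally. For infection, the stated analysis estimates density times prevalence: a ratio of 0.40 at the planning densities with no change in infection per mosquito, whatever the prevalence. For CI, the error equals the change in containers per house, 0.70 in the assumed example. For PPP the label is wrong but the numerical effect is negligible.

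This rests on aspiration time and houses per cluster being as planned. Missed houses or uneven aspiration would make the identities approximate without removing the problem. The 0.40 also takes the planning densities at face value; in general the spurious ratio equals the density ratio achieved.

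A reader might infer that the secondary analyses fail as a whole or that the trial's main result is at risk. Neither follows: the primary outcome is unaffected, and so are the HI, BI and PPH ratios. It is a limited correction, worth making because infection rate is named in the first main hypothesis.

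**What to change.** In the Secondary outcomes paragraph, and to match in the abstract, state that each outcome uses the denominator in its own definition:

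- **HI and CI:** cluster-level binomial-type model allowing overdispersion, with houses and containers as denominators.
- **BI and PPH:** negative binomial with log(houses) as offset.
- **PPP:** negative binomial with log(persons) as offset.
- **Infection:** rate per female tested, from a pooled-prevalence likelihood that uses pool sizes, with follow-up pools kept within cluster and survey. Report an estimate with its interval. If infected females per house is also reported, label it as that.

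The cost is slightly more analysis work, possibly more and smaller pools to test, and an infection estimate that will be openly imprecise because catches are small: at the planning densities about 0.25 × 40 × 3 × 10 = 300 control females and 0.10 × 40 × 3 × 10 = 120 per intervention arm. Container numbers are already recorded; PPP as defined needs household members counted in the surveyed houses. The pooling rule has to be set before the follow-up pools are made up. The Trial status section reports only baseline collection and allocation as complete, so at that stage there was still time.

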#### Missing data

Missing data will be reported as recommended by Díaz-Ordaz et al. [57] and their impact may be explored in secondary analyses.

### Data monitoring

In accordance with the findings of Grant et al., we have not established a Data Safety Monitoring Board for this study as it is not a “clinical trial evaluating a therapy with a mortality or irreversible morbidity endpoint” [58]. However, a Technical Steering Committee (TSC) was established which will meet at least every 6 months and address any safety or other concerns that may arise. The TSC will have one member from each of the partner organizations including the government and WHO. HC and CHW staff have been advised to contact MC staff should any adverse event be detected through passive monitoring as a result of project activities. CHW monthly monitoring forms will also record any adverse events (such as tingling in the hands after touching PPF or gastrointestinal effects after potential exposure of PPF to the mouth) that are reported. Any event will be promptly reported to the ethics committees and government partners. If an end to the trial is needed, the decision will come from the chair of the TSC. However, no harms are foreseen, and trials of similar products have not experienced any adverse events or unintended effects [16, 17].

### Access to data

All co-principal investigators and partners will be given access to the cleaned datasets without identifiers, which will be stored on the Malaria Consortium Sharepoint site and will be password protected. The final dataset will also be stored in the Cambodian National Center for Parasitology, Entomology, and Malaria Control central repository.

### Ancillary and post-trial care

In the event of any harm associated with the protocol MC will be responsible as the trial sponsor. The control group will be receiving routine interventions from CNM as described above and will continue to receive them after the close of the project. After the end of the project the lead institution, MC, will continue to advocate for, and encourage uptake of, any policy recommendations that come from the study.

### Dissemination policy

The principal investigator ([name]) will ensure that the results of the trial are published regardless of outcome. At least every 6 months results will be shared with the Technical Steering Committee. In addition to reporting the results in peer-reviewed journals, the results will disseminated at the provincial level and national level to all project stakeholders. All documents and study materials will be made available in a tool kit that will be given to all government stakeholders and partners. The investigators will also disseminate their findings in international scientific conferences. Reporting will follow the guidelines in the Consolidated Standards of Reporting Trials (CONSORT) Statement [59]. Authorship will follow MC authorship guidelines which require substantive contributions to the design, conduct, interpretation, and reporting of a trial. The full protocol, household-level dataset, and statistical code will placed in the Cambodian Ministry of Health’s central repository within 6 months of completion where all interested researchers can request access.

## Discussion

Due to the rise in dengue cases [3] and the current lack of effective vaccines and therapeutics, there is an urgent need to develop more effective vector-control methods [22]. These methods together with the development of new vaccines [12], genetic control of mosquitoes [14, 15], and new therapeutic drugs [60] will be essential in reducing dengue prevalence throughout the world. Additionally, evidence suggests that the main vector-control tool in Cambodia (temephos) is becoming less effective [19, 20], and a need to assess new sustainable vector-control methods in this context exists [22].

Recent studies have suggested the use of larvivorous fish to be effective in vector control [21, 22]; however, many were methodologically flawed and none have used a randomized controlled design [37]. The studies on previous products similar to Sumilarv® 2MR showed positive results [16, 17]; however, the new product has not been tested externally beyond small ongoing semi-field trials in Thailand (personal communication, [name], 2015). Evidence from larger trials is essential when trying to understand the true impact of these vector-control tools and in making recommendations to government bodies and donors.

The study area is suitable for the current trial as the disease is prevalent in the selected districts, and the province has a history of dengue outbreaks [20]. The study team is also familiar with the area having conducted multiple dengue research projects in the area, and have good relationships with the local authorities and communities in the area.

It would be preferable to have a primary outcome directly related to dengue incidence rather than an entomological one. Finding the appropriate metric to measure disease impact is bedeviled by the effect of human movement on patterns of transmission, and the pronounced temporal and spatial heterogeneity in transmission, which will necessitate very large cluster randomized study designs. We considered passive surveillance for dengue with rapid diagnostic tests in HCs. Although sensitivity among currently available tests was considered acceptable for routine clinical diagnostics [61] it was not considered high enough for seroconversion studies. No studies had used rapid diagnostics to estimate seroprevalence. Therefore, more expensive and labor-intensive efforts were preferable, such as cohort studies or capture-recapture methods (which have their own limitations [62]) to estimate the true number of cases, and using a more sensitive diagnostic tool such as RT-PCR. However, due to budget limitations it was not possible to employ them. Additionally, unpublished data from a recent cohort study in the proposed districts suggest that, given similar number of cases during this study timeframe, and the resources available to the current project, there would not be enough statistical power to show an impact of the likely size on case numbers. (personal communication, [name], 2015). Therefore, the endpoint chosen was the density of adult *Aedes* mosquitoes, which are on the causal pathway to disease.

There is always a need to balance potential benefits and harms during a trial. The potential benefits of the trial are substantial, and trials of similar interventions in the past have not experienced any adverse events or unintended effects [16, 17, 21, 22]. Additionally, because of the low acute toxicity of PPF it is considered extremely safe and is recommended by the WHO for use in drinking water [44].

This trial is designed to measure the reduction in adult and juvenile mosquitoes due to these vector-control methods relative to a control. However, one limitation is that the study was powered to detect a statistically significant difference between each arm compared with the control, and not between the intervention arms. This reduces the ability to see the impact of the PPF. A possible source of bias may be not having data collectors blind to the intervention; however, in this case it is unavoidable as data collection teams will be able to see the interventions in the containers which they sample. Contamination (spillover) of COMBI activities from intervention villages could affect our study by increasing knowledge or use of guppy fish in control areas. However, in the previous study it was found that only about 5% of containers had guppies in the control area at the end of the project [22]. Measurements of guppy fish coverage will also be conducted in control villages to identify the extent of any contamination.

Although these data are being collected within one province in Cambodia, it is likely that the result of this trial could be generalizable to areas with similar ecology within the country and in neighboring countries. Each country or province will have to make its own decision based on individual contexts. For example, unpublished MC studies in Myanmar showed similar size and types of containers and community practices in two regions, and interest from government officials in introducing guppies to water containers in response to dengue outbreaks (personal communication, [name], 2015). However, the decision was made to not introduce guppies in the Philippines as the community acceptance was low and the cool climate in higher altitudes was not suitable for guppy survival and reproduction (personal communication, [name], 2015).

### Trial status

At the time of submission of this manuscript the trial had completed the baseline data collections, enrollment of villages, and randomized allocation of the villages to three study arms.

